#### Subscale administered before each session

The four items version of the PSS [39] will be administered at the start of each session. These items have proven sensitivity to short-term changes in stress [40]. For the purpose of this study, the indicated timespan was changed from ‘In the last month’ to ‘In the last week’ to match the other pre-sessions measures for possible predictors. An example item is ‘In the last week, how often have you felt that things were going your way?’ These items will be scored on a VAS-scale of exact 10 cm by placing a cross on a line from 0 (not at all) to 100 (completely). Mean scores will be calculated, ranging from 0 to 100.

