#### Subscale ‘impulsivity’ administered before each session

As a proxy of emotion regulation, the subscale ‘Impulsivity’ will be used, comprising three items from the ‘Difficulties in Emotion Regulation Scale’ (DERS-18; 40). For the purpose of this study, the phrase ‘In the last week I have felt:’ was added to match the other pre-session measures for possible predictors. Example item: ‘When I am upset, I become out of control’. Items will be scored on a VAS-scale ranging from 0 (not at all) to 100 (completely)*.* Mean scores will be calculated, ranging from 0 to 100.

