#### Mood—measured before each session

Mood will be measured using a validated single item measure [44]. For the purpose of this study, we have altered the item ‘At the moment I feel’ to ‘In the last week I felt’ to make the timespan congruent to the other pre-session measures for possible predictors. This mood item will be scored on a VAS-scale ranging from 0 (sad) to 100 (happy). Mean scores will be calculated, ranging from 0 to 100.

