### Statistical analysis

First, multiple regression analyses and logistic regression analyses will be performed to examine whether high perceived daily stress, emotion dysregulation and low mood at baseline predict drop-out, no-show and treatment outcomes. Secondly, the concurrent association between each possible predictor measured prior to each session (i.e. perceived daily stress, emotion regulation and mood) and PTSD symptoms will be examined using bivariate (multilevel) growth modelling, as multiple observations of the predictor variables and PTSD symptoms (level 1) are nested within individuals (level 2) [49]. In order to infer that change in the predictor variables leads to change in PTSD symptoms, we will examine the timeline (i.e. temporal precedence) in two ways [50, 51]. The dynamic (i.e. temporal) associations will be examined by estimating whether change in PTSD symptoms from the previous week to the current week (t) can be predicted by change of a possible predictor at the previous week (t-1) using multilevel modelling. To examine the timeline of larger shifts instead of week-to-week changes, it will be examined whether the earliest significant decrease in mean levels of each possible predictor (improvement) occurs before the largest reduction in mean levels of PTSD symptoms.

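### The rule for dating larger shifts counts a decrease in every predictor as improvement, but on the mood scale as scored a decrease is worsening

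*Protocol article*

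**What the plan says.** The Statistical analysis section of the protocol article identifies the predictors as "each possible predictor measured prior to each session (i.e. perceived daily stress, emotion regulation and mood". To support an inference that predictor change leads to PTSD change, it describes two checks of timing. The first is a week-to-week lagged multilevel model. The second concerns larger shifts: it locates "the earliest significant decrease in mean levels of each possible predictor (improvement" and asks whether this event "occurs before the largest reduction in mean levels of PTSD symptoms". One rule serves all predictors, and mood is not set apart.

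The section on the mood measure fixes its direction: "This mood item will be scored on a VAS-scale ranging from 0 (sad) to 100 (happy". It then says "Mean scores will be calculated, ranging from 0 to 100", with no mention of reversal.

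The hypotheses at the end of the Background treat low mood as the adverse state, alongside high stress. Hypothesis 3 speaks of a reduction for stress but of an improvement for mood.

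**The concern.** The rule has two parts that must agree: an operation (find a significant decrease) and a meaning (improvement). On a scale where a higher score means happier, they disagree. An analyst who codes the operation as written will search the mood series for the first session at which patients were significantly sadder, and compare that date with the largest PTSD reduction.

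The check bears on hypothesis 4, that change in the predictors precedes later change in PTSD symptoms. Under the literal rule, a real and early gain in mood would go undated, and a real decline would be dated and labelled an improvement. Either would give the wrong answer for mood on this check.

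**Working it through.** The plan gives no figure to reproduce here. The main check sets each per-session scale beside the rule.

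| Predictor | Scoring in the article | Meaning of a decrease | Agrees with the label? |
|---|---|---|---|
| Emotion regulation (impulsivity subscale) | 0 to 100, higher is worse; example item "When I am upset, I become out of control" | Improvement | Yes |
| Perceived daily stress (four-item PSS) | 0 to 100, named as a stress score | Improvement, if scored as its name says | Yes |
| Mood (single item) | 0 (sad) to 100 (happy) | Worsening | **No** |

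No section of the article reverses mood or exempts it from the rule, so the contradiction follows from the text alone.

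**Which analyses use the rule**
- Baseline regressions, bivariate growth models, lagged week-to-week model: none uses it. Reversing mood there changes the sign of its coefficients and nothing else.
- Larger-shifts check: uses it, for mood as for the other two.

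**Illustration of the literal rule**

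Inputs from the article: 80 participants (Participants section) and 12 to 16 sessions (Methods), with 14 used.

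Assumed, because the article does not give them: starting mean 40; between-person and within-person SD 15 each; linear change from T0 to the last session; each session compared with T0 by a paired t-test at two-sided 0.05; no multiplicity correction; 2,000 simulated trials per setting.

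Formula at each session: t = mean(d) / (SD(d)/√80), where d is the session score minus the T0 score. The person effect cancels, so SD(d) = √2 × 15 = 21.2 and the standard error is 21.2/8.94 = 2.37 points. A 10-point gain at the last session is thus 10/2.37 = 4.2 standard errors above zero, and a test for a decrease cannot see it.

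| True change in mood | Trials with any significant decrease (rule as written) | Trials with any significant increase |
|---|---|---|
| +5 | 4.0% | 80.4% |
| +10 | 1.9% | 100% |
| +20 | 0.5% | 100% |
| 0 | 17.4% | 16.8% |
| −10 | 99.9% | 1.9% |

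The row for no change reflects the assumed uncorrected testing at 14 sessions, not the direction error.

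A second simulation used 13 occasions, 50 to 80 patients, 60% of variance between persons and a linear gain of 0.4 to 0.8 SD. A decrease from baseline appeared in 0.5–2.5% of trials and an increase in 97–100%. When successive sessions were compared instead, a chance decrease appeared in 5–15%. The article does not say which comparison is meant.

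**The case against.** The strongest reply is that the intent is plain. The rule carries the word improvement in parentheses, the same section speaks of low mood as the predictor, and hypothesis 3 asks for improvement in mood. On that reading, decrease is shorthand for a fall in problem severity. The article is similarly loose with emotion regulation, whose score is in fact impulsivity. A sensible analyst would notice, and recoding mood is a detail that the full plan may contain. This stands as far as intent goes: it is most likely a drafting slip. It does not remove the point, because the article does not leave the direction open. It states an operation that conflicts with its own scale.

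It is also fair that the simulation proves nothing by itself. Looking for decreases in a series built to rise must give few hits, and the percentages depend on assumed SDs, trajectory and test.

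Three stronger readings are tempting and are not supported.
- A reader might infer that mood will be wrongly reported as not leading PTSD change. That requires an analyst to follow one cue and ignore the label beside it.
- A reader might infer that the four-item PSS has the same fault, since its example item, "how often have you felt that things were going your way", is positively worded. But the article does not say that items are left unreversed. Reversing such items is routine scoring that an article may omit. The full PSS and DERS-18 are not the per-session scores to which this rule applies.
- A reader might infer that all session-level analyses are compromised. Only this check uses the rule.

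**Conclusion.** The point holds in a narrow form. For mood, the larger-shifts rule as worded contradicts both its own label and the scale on which mood is scored. Followed literally, it would date deterioration instead of improvement. This affects one of three predictors in one of two timing checks for hypothesis 4.

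The conclusion about direction rests only on the article's text. The simulated percentages show what a literal reading would do under assumed inputs and are not an estimate of the effect on this trial. The conclusion would fall away if the full plan, which is not shown, reverses mood before this analysis. The article's sentence would still need to say so.

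**What to change.** Change the last sentence of the Statistical analysis section in one of two ways:
- define the event as the earliest significant improvement, meaning a decrease for perceived stress and impulsivity and an increase for mood; or
- keep the decrease and state that mood is reversed beforehand (100 minus the score, labelled low mood).

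Either is enough, and the other analyses need no change. The cost is one sentence and no new data. The Discussion says that no data have yet been analysed, so the direction can be fixed before any result is seen.

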## Methods

This study follows a repeated measures observational design with baseline assessments, repeated measures over the course of treatment and post-treatment assessments. Twelve to sixteen sessions of NET will be provided to all patients included in the study. Various questionnaires will be administered at baseline (T0, pre-treatment), 1 week after NET completion (T1, post-treatment) and 6 weeks after NET completion (T2, follow-up). In addition, assessments to measure potential processes of change will be performed at the start of each NET session. See Fig. 1 for a detailed overview of the planned design and administered measures.

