### Participants

The study will take place at an outpatient clinic specialized in mental health care for refugees, asylum seekers, victims of sexual exploitation and otherwise traumatized populations in the Capital region in the Netherlands. The study aims to include 80 participants, in order to detect medium to small effect sizes [35]. Patients are referred to the clinic by a general practitioner or by a partnering social welfare organization. Patients’ background/nationality is diverse; most originate from West Africa, the Middle East and Eastern Europe. Their legal status varies from having obtained a residence permit or even Dutch citizenship to illegal residence in the country, and they may reside in asylum seekers centres, specialized shelters for victims of sexual exploitation, governmental shelters for illegal persons or live independently.

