### Data collection, management and analysis

#### Procedure pre-session measures

During baseline (T0) and at the start of each TFT session, the patient’s fixed practitioner or a supervised master’s level psychology student will administer the thirteen items selected to assess the four abovementioned possible predictors. To avoid an order effect, the sequence of the measures for possible predictors and the order of questions within every measure will change with every session. These measures will only be administered during the treatment period. They will be administered by pen and paper and are expected to take on average 10 min. Questionnaires are translated from their original English version according a forward-backward procedure by two independent native speakers into Dutch, and by professional translators into Arabic, French, Amharic and Tigrinya. Interpreters will assist for other languages.

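### The larger-shifts timing rule sets the predictor's earliest significant fall against PTSD's largest fall, so it is biased towards predictor first and cannot support the stated inference about direction

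*Protocol article*

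**What the plan says.** The protocol article's Statistical analysis section gives the purpose of the timing analyses: "In order to infer that change in the predictor variables leads to change in PTSD symptoms, we will examine the timeline". Two are named.

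- A week-to-week multilevel model, in which change in PTSD "can be predicted by change of a possible predictor at the previous week (t-1) using multilevel modelling".
- An analysis of larger shifts, which asks whether "the earliest significant decrease in mean levels of each possible predictor (improvement) occurs before the largest reduction in mean levels of PTSD symptoms".

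The section does not state the reverse comparison (PTSD's earliest fall against the predictor's largest). It does not say whether a fall is counted from baseline or from the previous session, and it gives no benchmark for how often the rule would be met by chance.

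The series are the short measures taken "During baseline (T0) and at the start of each TFT session". On the mood item (Measurements, Mood) 0 is sad and 100 is happy, so a higher score is better.

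**The concern.** The two series are dated by different events. The first significant fall tends to come early in a declining series. The largest single fall can come at any session, and in a steady decline its position is mostly noise. The variable given the earliest criterion therefore has a head start, and the protocol gives it to the hypothesised cause. Exchanging the labels would favour the opposite conclusion.

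This is one of only two analyses offered for temporal precedence, the subject of hypothesis 4 in the Background. The Discussion links the findings to preparatory modules before NET and to treatment indication, so a lead produced by the rule itself could be carried into practice.

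There is also a point of wording. Read literally, a decrease in the mood score is a worsening.

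**Working it through.** The document gives no figure for this rule, so there is nothing to reproduce. The check is a logical step followed by a simulation.

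**Logic.** For a series X let E(X) be the session of its first significant fall and L(X) the session of its largest fall. The rule declares precedence when E(predictor) < L(PTSD). Put the same series on both sides. If its largest fall is significant and both falls use the same reference, then E(X) ≤ L(X) always, because the largest fall is itself one of the candidates for earliest. The rule can thus find that a series precedes itself, and can never find the reverse.

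**Inputs from the document.**
- 80 participants (Participants).
- 12 to 16 sessions (Methods) plus T0, so 13 to 17 occasions; 15 is used below.
- Total decline of 0.25, 0.63 and 1.01 SD. The Background gives g = .25–1.01 for trauma-focused therapy in refugee populations; 0.63 is the midpoint, (0.25 + 1.01)/2. The range is borrowed and is not a forecast for this trial.

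**Assumptions not in the document.** Predictor and PTSD share one mean curve with no lead or lag; intraclass correlation 0.5 to 0.7; AR(1) 0.3; correlation between series 0.5; paired t-tests at two-sided 0.05; PTSD's largest reduction is the largest session-to-session fall in the mean. The predictor's significant fall is read two ways: from baseline, and from the previous session.

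**Result.** Percentage of trials in which the rule is met although neither series leads (range over the two intraclass correlations):

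| Curve | From baseline, 0.63 SD | From baseline, 1.01 SD | Session to session, 0.63 SD | Session to session, 1.01 SD |
|---|---|---|---|---|
| Linear | 61-68 | 73-77 | 30-38 | 46-59 |
| Late | 60-73 | 83-90 | 31-43 | 55-73 |
| Sigmoid | 57-65 | 77-84 | 35-49 | 58-72 |
| Front-loaded | 51 | 47-50 | 33-37 | 42-44 |
| Single step | 10-13 | 11 | 15 | 14-15 |

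- At 0.25 SD the rate is 12-45% from baseline and 17-20% session to session. In the session-to-session case about half of the trials show no significant fall at all, except with the step curve. From baseline, with late and sigmoid curves, the predictor comes after PTSD more often (42-48%) than before it (22-34%).
- From baseline at 1.01 SD, leaving out the step, before is found in 47-90% and after in 3-12%.
- The swapped rule (PTSD before predictor) is met about equally often. Both directions are met in the same trial in 25-52% (0.63 SD) and 24-84% (1.01 SD) from baseline, and in 5-16% and 15-54% session to session, again without the step.
- At least one of three predictors meets the rule in 52-93% (from baseline, 0.63 to 1.01 SD, without the step).

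**A second set of assumptions.** 14 occasions and a linear 20-point fall on the 0-100 scale, with between-person SD 15 and within-person SD 12. Total SD = √(15² + 12²) = √369 = 19.2, so the fall is 20/19.2 = 1.04 SD. Over repeat runs the rule is met in 76-78% from baseline and 55-56% session to session; the reverse in 78-79% and 57-59%; both at once in 59-62% and 25%.

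**Same criterion on both sides.** Linear fall of 0.8 SD, 13 occasions, correlation 0.5; before/tie/after:
- protocol's mixed rule, from baseline: 68/16/16%
- largest against largest: 38/27/35%
- earliest against earliest: 35/32/32%

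The tilt disappears once the criterion is shared.

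**The case against.** A reader might infer that the rule usually shows precedence when there is none, or that it confirms hypothesis 4 by construction. The documents do not support either statement. The frequency depends on curve shape, size of decline and reference point, and none of these is fixed. The stated target is larger shifts, and a straight line contains none. With one abrupt shift and no lead, the rule is met in only 8-16% of trials and mostly gives ties. Near 0.25 SD, the low end of the Background's range, it is met in 11-45%.

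A reader might also infer that the rule credits the predictor even when PTSD truly leads. With a two-session PTSD lead that happens in 59-60% (from baseline) and 43-48% (session to session), but for a linear decline only. With front-loaded or sigmoid curves it is 11-32%, and with a step 9-14%.

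Three further objections stand. The lagged multilevel model addresses hypothesis 4 directly and does not use this rule. The text does not say that the means are raw means of those still attending, so a drift caused by changing composition cannot be read into it. The bracketed word improvement makes the intent for mood clear, so that is a wording correction.

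What does not stand is the suggestion that this is detail left to a fuller plan. The rule is stated, and it treats the two series differently. The section cites sources for its approach that are not at hand, but the rule has to be judged as written here.

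**Conclusion.** The concern holds in limited form, and the rule is wrong as written. It is biased towards predictor first when declines are gradual and of moderate or larger size. With neither series leading, it is met in about half or more of trials at about 0.6 SD and above from baseline, and session to session mainly near 1 SD. For small declines or an abrupt shift the rate is much lower. These frequencies rest on the assumed curves, correlations and test level, and the front-loaded figures also on how steep the early fall is.

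The conclusion about inference does not depend on the exact rate. A rule that can be met in both directions in the same data, and is tested in only one, does not discriminate direction. A positive result would not support the claim about what leads to what. The defect is confined to the larger-shifts analysis.

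**What to change.** Before analysis, restate the rule as follows.

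1. Apply the same criterion and the same reference point to both mean series: earliest against earliest, and largest against largest.
2. Report the reverse comparison alongside.
3. Give a confidence interval for the difference in timing by resampling patients and re-estimating the session means in each resample. Claim precedence only if the interval excludes zero.
4. Replace decrease with improvement, and define it for mood as an increase.

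The comparison should stay on the mean series. Each patient has one score per measure per session, so an earliest significant fall is undefined within a patient unless a further threshold is added.

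The cost is some wording and slightly more analysis, with no new data. The Discussion states that no data analysis has yet been performed, so the change can be fixed in advance. The downside for the investigators is that a favourable result becomes less likely. Timing also moves in whole sessions, so the interval will be coarse and, for a gradual decline, probably wide.

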## Discussion

Among the growing number of forcibly displaced people worldwide, many are suffering from trauma-related mental health problems. As psychological treatments for displaced persons with PTSD appear to be less successful than for other populations, insight is needed in factors that affect the feasibility of these treatments. However, relevant research is lacking. The ongoing trial presented in this paper is the first to examine the interplay of factors for feasibility and effectiveness of in displaced victims of interpersonal violence receiving NET. More specifically, the impact of perceived daily stress, emotion dysregulation, and disturbed mood on PTSD symptom changes during TFT are examined.

The theoretical basis of NET has been well documented, and its effectiveness has been examined in various studies and contexts [33, 34, 36]. Yet, specific factors contributing to positive outcomes or constraining its feasibility are largely unidentified. In the current study, repeated measures will identify various constructs relevant for treatment feasibility and response of NET. Since, to our knowledge, this is the first study to use repeated measures within the target population, findings will additionally provide insight into the feasibility of this method for displaced populations.

As the method requires only minor adaptations to usual treatment proceedings and follows an observational design, participants can be included that might have to be excluded in more complex designs [52]. This allows for conclusions based on a sample representing the intended population with high external validity, which is exceptional for this specific group [53]. Although our design favours generalizability of the results, it may reduce the internal validity of the study; for instance, the present design does not allow for the examination of the extent to which observed changes in PTSD can be attributed to NET, but to factors such as natural recovery, bias or confounders. However, as we aim to study factors promoting or constraining treatment feasibility, a naturalistic design is the most ethical, feasible and time-efficient design to obtain answers to our research questions. Besides, the reduced internal validity is partially addressed by limiting the possibly confounding role of concurrent treatment.

Evidently, there are factors possibly impacting treatment response. For the purpose of this study, repeated measures were selected on the basis of relevant studies [41, 44] and clinical insights. Thus, the set of questions have been tailored to the specific characteristics of the study population. Conclusions drawn from the study therefore may hold relevant implications in clinical practice for displaced victims of interpersonal violence. Although the chosen subscales support the clinical validity of the study, the PTSD and emotion dysregulation subscales have not been validated as weekly repeated measures.

It is important to note that inclusion for the current study has already started; however, it is planned to run until early 2021. Critically, no data analysis has currently been performed yet.

We expect that the findings of this study will contribute to both the scientific and the clinical field. Identifying factors that limit treatment response may in turn inform the development of improved treatment modules that specifically address these blockages. The promotion of self-efficacy or problem-solving skills prior to NET, for example, may decrease perceived daily stress and its constraining effect on the feasibility of NET. Likewise, promoting emotion regulation prior to NET may intensify its potential supportive role for TFT. Additionally, if these factors have no predictive value for the course of PTSD during treatment, clinicians might be encouraged to offer TFT to patients despite the presence of daily stressors, emotion regulation difficulties and mood problems. By identifying predictors of treatment response, the current study can enable treatment indications to be tailored to individual characteristics.

Furthermore, exploring these predictors sheds a broader light on the consequences of trauma, beyond a narrow focus on PTSD, and may provide clues for a wider range of relevant treatment foci. In this way, this study responds to the ongoing debate on the emphasis focus of PTSD in designing treatments for displaced populations [10].

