**Discussion:**

The present study is the first to examine the interplay of facilitating and interfering factors possibly impacting treatment feasibility and effectiveness in displaced victims of interpersonal violence with PTSD receiving NET, using repeated measures. The current study can help to improve future treatment based on individual characteristics.

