In the present paper, the feasibility, rationale and protocol of an ongoing trial are described. Specifically, we aim to identify relevant predictors of PTSD symptom change during and after NET in 80 displaced victims of interpersonal violence. The primary hypotheses of the study are (1) it is feasible to administer highly repeated measures, within a diverse group of displaced persons. (2) High perceived daily stress, emotion dysregulation, and low mood at baseline and during NET predict higher drop-out, higher no-show and poorer treatment response of NET (i.e. less PTSD symptom reduction), thus undermining the feasibility of NET; (3) Reduction in perceived daily stress and improvement in emotion regulation and mood during NET are associated with concurrent reductions in PTSD symptoms during NET; (4) Change in perceived daily stress, emotion dysregulation, and mood during NET predict subsequent changes in PTSD symptoms at later stages of NET. Furthermore, the study aims to establish whether NET contributes to positive aspects of mental health.

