#### Inclusion criteria

Patients will be included in the study if they are displaced victims of interpersonal violence, aged 18 years or older, if they have PTSD as a primary diagnosis established by a psychiatrist or clinical psychologist during intake, if individual NET in an outpatient setting has been indicated for them and if they are cognitively able to give informed consent to participate in the study.

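### With every participant on NET and no comparator, a predictor of PTSD change cannot be separated from a purely prognostic factor, so the Discussion's claim about tailoring treatment indications does not follow

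*Protocol article*

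**What the plan says.** The Methods section describes one treated group: "This study follows a repeated measures observational design with baseline assessments, repeated measures over the course of treatment and post-treatment assessments", and "Twelve to sixteen sessions of NET will be provided to all patients included in the study". The inclusion criteria admit patients only "if individual NET in an outpatient setting has been indicated for them". No comparison group appears anywhere in the article.

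The second hypothesis (Background) is that high stress, poor emotion regulation and low mood "predict higher drop-out, higher no-show and poorer treatment response of NET". The Statistical analysis section addresses this with multiple and logistic regressions within the treated group. It then adds multilevel models of concurrent and lagged associations between the session-by-session measures and PTSD symptoms.

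The Discussion concedes that "the present design does not allow for the examination of the extent to which observed changes in PTSD can be attributed to NET", and names spontaneous improvement, bias and confounding as rival explanations. Further on it states: "By identifying predictors of treatment response, the current study can enable treatment indications to be tailored to individual characteristics". Just before that, it suggests that if the factors turn out not to predict the course of PTSD, clinicians may feel encouraged to offer trauma-focused therapy (TFT) to patients who have these difficulties. The abstract is looser: "The current study can help to improve future treatment based on individual characteristics".

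**The concern.** Choosing for whom a treatment is indicated requires evidence that its benefit, relative to not giving it or giving something else, differs with the patient characteristic. A regression within one treated group shows only that outcome under treatment differs. Patients with high stress might improve less under NET because NET helps them less. They might also improve less whatever they receive. The concession in the Discussion about average change applies equally to differences in change between patients: if the change cannot be attributed to NET, neither can a gradient in that change.

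At stake is how the results are used. A factor that merely marks a poorer course could be reported as a reason to time or offer NET differently, although those patients may gain as much as others, or more. A flat association could be taken as evidence of equal benefit when it is not.

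**Working it through.** The article gives no figure that tests this point. It states only that "The study aims to include 80 participants, in order to detect medium to small effect sizes", without a significance level, power or numerical effect size. The check is therefore one of identifiability.

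**Set-up.** Let x be a baseline predictor in SD units (say, perceived stress) and y the PTSD symptom reduction, higher being better. All numbers below are assumptions chosen for illustration.

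- Outcome with NET: y1 = 1.0 + b1·x + e
- Outcome without NET: y0 = 0.3 + b0·x + e
- Benefit of NET at x: (1.0 - 0.3) + (b1 - b0)·x = 0.7 + (b1 - b0)·x

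The study observes y1 only. It can estimate b1. It contains no information on b0.

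**Positive association.** Hold b1 at -0.30 and vary b0:

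| Scenario | b1 (observable) | b0 (not observable) | Benefit at x = -1 | x = 0 | x = +1 |
|---|---|---|---|---|---|
| A. Purely prognostic | -0.30 | -0.30 | 0.7 | 0.7 | 0.7 |
| B. Less benefit at high x | -0.30 | 0 | 1.0 | 0.7 | 0.4 |
| C. More benefit at high x | -0.30 | -0.60 | 0.4 | 0.7 | 1.0 |

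For example, in C at x = +1 the benefit is 0.7 + (-0.30 + 0.60)·1 = 1.0. Simulating the three scenarios with 400,000 patients each gave slopes under NET of -0.300, -0.301 and -0.300: the same data pattern with opposite implications for indication. In C the patients with the worst outcome under NET gain the most from it.

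**Null association.** Set b1 = 0. The benefit is then 0.7 - b0·x. With b0 = 0 it is 0.7 throughout. With b0 = -0.30 it is 0.4/0.7/1.0 at x = -1/0/+1. With b0 = +0.30 it is 1.0/0.7/0.4. A flat slope under NET is compatible with all three.

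**Sample size.** A larger N sharpens b1 and leaves b0 unknown, so the ambiguity is the same at 80 patients as at any other number.

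**Could another planned element supply b0?**

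- The Recruitment section describes a wait of 1 to 4 months before NET. Baseline (T0) is taken when patients are called to start, after that wait, so no untreated course is measured.
- The lagged models address which change comes first within patients on NET. Temporal order does not provide a course without NET.
- A statistical analysis plan not shown here could not add a comparator to a single-group design.

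**The case against.** Several points on the other side have force.

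- The tailoring sentence is a forward-looking expectation in a Discussion, not a pre-specified conclusion. None of the planned analyses is presented as a test of differential benefit, and the Background defines poorer response simply as less symptom reduction. This stands. It limits the remedy to wording but does not make the sentence follow from the design.
- The limitation in the Discussion is study-wide, with attribution to NET given as one example. A reader might infer that the following sentence exempts the predictor question. The text does not say so: it defends the naturalistic design on ethical and practical grounds and calls the loss of internal validity only partly addressed. What can be said is that the limit is not carried over to the predictor results.
- Drop-out is defined by departure from the NET protocol, so it has no counterpart without NET, and the argument that patients might do worse anyway does not apply to it. This stands. Associations with drop-out and no-show can be estimated here and may suggest where support around NET is needed. They still do not show who should receive NET rather than something else.
- The article does not propose steering patients away from NET, so part of the harm is inferred.
- It is tempting to quote how often a purely prognostic factor would reach significance with 80 patients. The article gives no correlation from which to compute this. Such a percentage would rest on an assumed value and would not test the claim.

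**Conclusion.** The claim that the study can support tailoring of treatment indications does not follow from a single group in which all patients are indicated for and given NET. The same holds for reading a null result as support for offering TFT. In the worked example, one observed slope fits a benefit at +1 SD anywhere from 0.4 to 1.0, around a mean of 0.7. Those values are illustrative; the ambiguity itself depends only on the absence of a comparator.

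A reader might go further and infer that any predictor found here is prognostic. The documents do not support that, because an association could still reflect a real difference in benefit. The defensible statement is that the two cannot be told apart. Nor does the point invalidate the planned analyses: hypotheses 2 to 4 are answerable as associations among patients receiving NET. The general limitation already in the Discussion lessens the problem but does not cure it.

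**What to change.** In the Discussion:

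1. Replace the tailoring sentence with a statement that the study identifies factors associated with the course of PTSD, drop-out and no-show among patients receiving NET, and that these may generate hypotheses about support around NET.
2. Qualify the null-result sentence in the same way: absence of association under NET does not show equal benefit from TFT.
3. Extend the existing limitation on attribution explicitly to the predictor results.
4. Add that conclusions on treatment indication would need a comparison group and a treatment-by-predictor interaction.

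The hypotheses, measures, sample size and planned analyses stay as they are. The abstract's sentence is loose enough to stand once the Discussion is corrected. The cost is a few sentences and a more modest claim. The article reports that no analysis had yet been done, so the interpretation can be settled before results are known.
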